### Statistical analysis

Univariate analyses using Student's test or non-parametric tests (quantitative data) and Khi^2 ^test or Fisher's exact test (qualitative data) will be performed to describe population characteristics [35].

Outcomes in all "control" and "intervention" units will be performed using multivariate analyses, adjusting on various potential confounding factors about patient characteristics. The variability of patients within the same cluster should be inferior to the inter-cluster variability. Outcomes will be assessed at the patient level by taking into account cluster effect using logistic regression. Evolution of intervention effect will be assessed by a modelling of chronological series unit by unit during the "intervention" time periods (figure 1) [36].

Only patient with at least one preoperative and one postoperative collected CAM will be analysed. An alpha level of 0.05 will be used to determine statistical significance. Data analysis will be performed using the analysis software SAS (version 9.1, SAS Institute Inc, Cary, USA).

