**Method/Design:**

Study design is a stepped wedge cluster randomized trial within 3 surgical wards of three French university hospitals. All patients aged 75 and older, and admitted for scheduled surgery will be included. The multifaceted program will be conducted by mobile geriatric team, including geriatric preoperative consultation, training of the surgical staff and implementation of the *Hospital Elder Life Program*, and morbidity and mortality conference related to delirium cases. The primary outcome is based on postoperative delirium rate within 7 days after surgery. This program is planned to be implemented along four successive time periods within all the surgical wards. Each one will be affected successively to the control arm and to the intervention arm of the trial and the order of program introduction within each surgical ward will be randomly assigned. Based on a 20% reduction of postoperative delirium rate (ICC = 0.25, α = 0.05, β = 0.1), three hundred sixty patients will be included i.e. thirty patients per service and per time period. Endpoints comparison between intervention and control arms of the trial will be performed by considering the cluster and time effects.

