## Methods/Design

### Study design

CONFUCIUS protocol is based on a stepped wedge trial design, which is appropriate in assessing the impact of patient safety interventions [23,24]. It is an original design of cluster randomised controlled trial (figure 1). In the CONFUCIUS trial, the multifaceted prevention program will be rolled-out sequentially to three surgical wards (clusters) over four time periods (steps). The order in which the different surgery wards will receive the program is determined at random, allowing the full implementation of intervention in all participating clusters by the end of the trial [24]. Stepped wedge design also has strong methodological value to reduce contamination bias, considering that each cluster acts as its own control and hence provides data in both control and intervention arms of the trial [24].

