### Sample size

Sample size calculation was inspired from the methodology of Hussey and Hughes [23] and based on the following hypothesis: 1/three surgical wards (clusters) over four successive time periods, 2/improvement of at least 20% regarding primary outcome after the program implementation (from 60% to 40%) [1,16,19], 3/alpha fixed at 5%, 4/a number of patients per time period ranging from 60 to 120, 5/a coefficient of variation or intracluster correlation coefficient (ICC) ranging from 0 to 0,4. The ICC is a measure of the relatedness of clustered data by comparing the variance within clusters with the variance between clusters. Table 2 presents the statistical power obtained according to various values for ICCs and numbers of patients per time period. At least 90 patients per time period, i.e. 30 per time period and per surgical ward will be necessary to obtain a statistical power greater than 90%. Consequently, 360 patients will be included in the study. The time period duration will be 6 months to ensure the inclusion of 30 patients per time period and per surgical ward.

**Table 2 T2:** Statistical power calculated from intracluster correlation coefficients (ICC) and numbers of patients per time period

ICC	60 patients per time period	90 patients per time period	120 patients per time period
**0**	0.95	0.99	1

**0.1**	0.87	0.96	0.99

**0.2**	0.84	0.95	0.98

**0.3**	0.83	0.94	0.98

**0.4**	0.83	0.94	0.98

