The CONFUCIUS study is based on an original methodology. Stepped wedge trial design is a particular cluster randomised controlled study design which is useful for evaluation of patient safety interventions [23,24]. This design differs from both parallel and cross-over designs. With stepped wedge design, intervention is introduced to participants sequentially so that, by the end of the study, all participants are exposed to the intervention [23,24]. The three main motivations for using a stepped wedge design are ethical, logistical and statistical [23,24]. (1) From an ethical point of view, if the hypothesis is that the intervention will do more good than harm, it might be considered unethical to exclude any participants from the program. (2) Stepped wedge design is also particularly useful when, for logistical reasons, it is not possible to implement an intervention to all participants simultaneously. (3) Furthermore the stepped wedge design has statistical advantages. First, surgical wards act as their own control and hence provide date points in both control and intervention units [23,24]. This feature of the stepped wedge design reduces the risk of bias, which may be most important in non-randomised studies. Second, the effects of time can be included in the statistical model, hence controlling for temporal changes in the effectiveness of the program [23,24].

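### The Statistical analysis section names a cluster effect but no calendar-period term for the control-versus-intervention comparison, while the Abstract promises cluster and time effects; the two must be reconciled

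*Protocol article*

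**What the plan says.** Three places in the protocol article bear on the comparison.

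- **Statistical analysis.** The model is given as "Outcomes will be assessed at the patient level by taking into account cluster effect using logistic regression", in multivariate analyses "adjusting on various potential confounding factors about patient characteristics". Period is not mentioned as a term. The section's one time element is separate: "Evolution of intervention effect will be assessed by a modelling of chronological series unit by unit during the" intervention periods.
- **Abstract, Method/Design.** "Endpoints comparison between intervention and control arms of the trial will be performed by considering the cluster and time effects".
- **Discussion.** Among the statistical advantages of the design, "the effects of time can be included in the statistical model, hence controlling for temporal changes in the effectiveness of the program".

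The design is "three surgical wards (clusters) over four successive time periods" (Sample size), each period lasting 6 months, with staggered roll-out "allowing the full implementation of intervention in all participating clusters by the end of the trial" (Study design).

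**The concern.** The section that sets out the model lists one of the two adjustments that a stepped wedge needs (cluster) and leaves out the other (period). The series model of how the effect evolves does not fill the gap: it is confined to intervention periods, uses no control data, and so cannot separate a background trend from the programme effect.

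Every ward moves from control to intervention and never back, so exposure is tied to calendar time. The trial spans 4 x 6 = 24 months. If delirium falls over that time for unrelated reasons, an analysis without period credits the fall to the programme. If recorded delirium rises, for instance because nurses detect it better, the same analysis hides a real benefit. An analyst who follows the Statistical analysis section literally would fit a different primary model from one who follows the Abstract.

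**Working it through.** **Inputs.** From the article: 3 wards, 4 periods, 30 patients per ward per period (360 in all), 60% delirium under control against 40% under the programme, alpha 5%, ICC 0.25 (Abstract). Assumed: a two-sided test (sidedness is not stated); one ward crossing at each of periods 2, 3 and 4 (Figure 1 is not shown), giving 6 control and 6 intervention units; residual variance 0.24 (= 0.6 x 0.4); and every size of secular trend, since the documents give none.

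**Step 1: how much later the intervention units are.** Mean intervention period minus mean control period, by ward:

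- crosses at period 2: (2+3+4)/3 - 1 = 2
- crosses at period 3: (3+4)/2 - (1+2)/2 = 2
- crosses at period 4: 4 - (1+2+3)/3 = 2

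With ward but not period in the model, a linear trend of d per period therefore appears as an effect of about 2d.

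**Step 2: bias on the risk-difference scale, no true effect, ICC 0.25.** The standard error of the cluster-only estimate is 0.0564.

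| Assumed fall per period | Spurious effect | False-positive rate |
|---|---|---|
| 2 points | -4.0 points | about 11% |
| 5 points | -10.0 points | about 42% |
| 10 points | -19.9 points | about 94% |

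The planned effect is 20 points.

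**Step 3: simulation of the logistic model.** 12 units of 30 patients, no true effect, starting risk 60%, assumed ward SD of 0.5 on the logit scale, linear logit drift.

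| Assumed drift over the trial | Type I error without period terms |
|---|---|
| none | 5% |
| 60% to 56% | 6% |
| 60% to 53% | 13% |
| 60% to 45% | 37% |
| 60% to 38% | 73% |

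With period terms, type I error is about 3-6% in every scenario. Repeat runs agree to within about two percentage points.

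**Step 4: what period adjustment does to precision.** For the Hussey-Hughes model with period effects, with I = 3 wards, T = 4 periods and s2 = 0.24/n:

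Var = I s2 (s2 + T t2) / [(I U - W) s2 + (U^2 + I T U - T W - I V) t2]

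The layout gives U = 6, W = 0+1+4+9 = 14 and V = 9+4+1 = 14, so the two brackets are 18 - 14 = 4 and 36 + 72 - 56 - 42 = 10. At ICC 0.25, t2 = 0.24 x 0.25/0.75 = 0.08.

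- n = 30 per ward per period: s2 = 0.008; Var = 0.024 x 0.328 / 0.832 = 0.00946; SE = 0.0973; power = Phi(0.20/0.0973 - 1.96) = 0.54.
- Same n without period effects: SE = 0.0564; power = Phi(0.20/0.0564 - 1.96) = 0.94.

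**Step 5: the plan's own power figures.** Table 2 prints 0.94-0.96 for 90 patients per period at ICC 0.1-0.4. A period-adjusted calculation with 60/90/120 split over the three wards (20/30/40 each) matches 0 of its 15 cells. A period-adjusted calculation with 60/90/120 entered per ward per period matches all 15 (largest difference 0.005, reading the ICC column as a coefficient of variation with between-ward SD = 0.6 x CV). A cluster-only calculation at 20/30/40 per ward matches at most 14: at ICC 0 and 60 patients it gives 0.885 against the printed 0.95.

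**The case against.** The strongest reply is that reading the model as cluster-only argues from silence. The Statistical analysis section does not say that time is excluded, the Abstract says outright that it will be considered, and the sample size is said to be inspired by the Hussey and Hughes method for stepped wedge trials. The article condenses a fuller protocol, where exact model terms are usually found. All of this stands as a limit on the claim: it shows an intention to model time, and the bias arises only if period is in fact omitted and a trend exists. It does not remove the conflict, because the article does specify the model, names one adjustment, and gives time a different role there.

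The magnitudes also rest on assumed drifts. With no drift the error rate is nominal, and with a slight drift it is close to nominal; the large figures need a large background fall.

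A reader might infer from the contrast of 94% with 54% that Table 2 was computed without period effects. The documents do not support that. The best match to Table 2 has period effects in the model and 60/90/120 counted per ward. That points to a separate sample-size problem and is not evidence that the planners left time out.

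**Conclusion.** The concern holds as an internal inconsistency with a real consequence. The Statistical analysis section and the Abstract describe different primary comparisons, and the Discussion is only permissive. Run as written, the former gives a contrast confounded with calendar time, biased by about 2d for a trend of d per period: half the planned effect at an assumed 5 points per period. Type I error then lies between about 5% and 73% over the assumed drifts, against about 3-6% with period terms. These figures depend on the assumed one-ward-per-step layout, the ward SD of 0.5 on the logit scale and the drift sizes. The stronger reading, that the trial has decided to ignore time, is not supported, because the Abstract commits to considering it.

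**What to change.** Bring the Statistical analysis section into line with the Abstract. State that the primary model includes intervention, ward and calendar period (for example categorical with 4 levels) over all 12 units, plus the patient covariates, and that period terms are also used for the secondary outcomes. Other codings of ward and period are possible; what matters is that period is named in the model for the main contrast.

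The wording change is small, but the cost is not confined to wording. The confidence interval widens, at ICC 0.25 from a standard error of 0.056 to 0.097, and the power in the Sample size section must be restated. A period-adjusted analysis at 30 per ward per period has about 54% power at ICC 0.25 (two-sided; about 66% one-sided), and 53% to 73% two-sided over ICC 0.4 to 0, against the stated figure above 90%. On the same assumptions, 90% power at ICC 0.25 would need about 76 per ward per period, that is 76 x 12 = 912 patients.

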**Figure 1 F1:**
[figure not shown]
**Design of the CONFUCIUS study**. One cluster (C1, C2 or C3) represents one surgical ward. One unit (control or intervention) represents one time period of one cluster. "White square": "control" unit = surgical wards without multifaceted prevention program "Black square": "intervention" unit = surgical wards with multifaceted prevention program

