### Setting and patients

The CONFUCIUS trial will take place in 3 surgical wards (orthopaedic, digestive and urology surgery) of 3 distinct French university hospitals. Each hospital benefits from its own MGT, which is composed of geriatricians and nurses. All health professionals in the participating surgical wards will be involved to conduct the multidisciplinary prevention program (i.e. surgeons, anaesthetists, nurses, and nurse assistants).

Inclusion criteria are age 75 and older, admission for a scheduled surgery (i.e. respectively colorectal cancer, ureterostomy, nephrectomy or cystectomy, total hip or knee replacement), participation agreement and no psychiatric trouble.

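### The evolution of the intervention effect is planned, read literally, on intervention units only, where a secular trend cannot be told apart from a changing effect

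*Protocol article*

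**What the plan says.** The Statistical analysis section describes two analyses of the outcomes.

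- **Main analysis:** "Outcomes in all 'control' and 'intervention' units will be performed using multivariate analyses", at patient level, "taking into account cluster effect using logistic regression".
- **Course of the effect over time:** "Evolution of intervention effect will be assessed by a modelling of chronological series unit by unit during the" intervention time periods, with a pointer to Figure 1 and to a cited method.

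The Figure 1 legend defines the term used in both: "One unit (control or intervention) represents one time period of one cluster". The design has three wards and four periods (Study design), hence 12 units, and "The time period duration will be 6 months" (Sample size).

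Time effects are mentioned in two other places. The Abstract (Method/Design) promises that cluster and time effects will be considered when the arms are compared. The Discussion says that a stepped wedge model can include time effects and so control for temporal changes. Neither place says how the evolution analysis is to separate calendar time from time since introduction.

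**The concern.** An intervention effect is a contrast with control. A series built only from units under the programme follows the delirium rate under the programme, and the rate moves for two kinds of reason: the programme matures or fades, or something else changes over calendar time. Within one ward both run on the same clock, shifted by that ward's start period.

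Four 6-month periods span two years, which leaves room for drift in case mix, practice or detection. Delirium is scored by ward nurses (Outcome measurement), and the Discussion itself expects ward staff to recognise delirium better. Such drift could be reported as the programme gaining or losing effect.

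**Working it through.** The document attaches no figure to this analysis, so there is none to reproduce. The check is whether the quantity can be estimated at all.

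**Inputs**
- 3 wards × 4 periods = 12 units (Study design), with 30 patients per unit (Sample size).
- Planned rates of 60% and 40% (Sample size). The binomial variance is 0.6 × 0.4 = 0.24 in both arms, so the variance of a unit's rate is 0.24/30 = 0.008.
- Assumed layout, as Figure 1 is not shown: one ward crosses at each of periods 2, 3 and 4. Intervention units are then 3 + 2 + 1 = 6, and control units are 6.
- Ward terms are kept, because the wards are "3 surgical wards (orthopaedic, digestive and urology surgery) of 3 distinct French university hospitals" and equal baseline rates are not credible.
- The scale is the risk difference, with fixed ward effects and least squares on unit rates.

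**Step 1. Intervention units only.** For ward *i* with start period *s_i*, time since introduction is *e* = *t* − *s_i*. Given the ward terms, *e* is therefore an exact linear function of *t*. The matrix with 3 ward terms, *e* and *t* on the 6 units has rank 4 for 5 columns. With categorical period in place of linear *t* the rank is 5 for 7 columns. The slope on *e* is not estimable in either case, so adding a period term does not repair the series. The collinearity within a ward does not depend on the order of crossover.

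**Step 2. What is reported if calendar time is left out.** Take a baseline of 60% in period 1, a constant effect of −20 points and a secular trend of −5 points per period. The expected rates in the intervention units are:

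| Ward starting in | Period 2 | Period 3 | Period 4 |
|---|---|---|---|
| Period 2 | 35% | 30% | 25% |
| Period 3 | – | 30% | 25% |
| Period 4 | – | – | 25% |

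With ward terms, the fitted slope on time since introduction is −5 points per period, although the effect never changes. With a trend of −2 the slope is −2. The whole trend is credited to the programme. If ward terms are dropped as well, half the trend still leaks in (−2.5 and −1.0).

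**Step 3. All 12 units.** The terms are intercept, 2 ward, 3 period, intervention, and intervention × periods since introduction (0, 1, 2), which makes 8 columns. The rank is 8. On the same noise-free rates the model returns an effect of −20 points and a slope of 0 under both trends.

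**Step 4. Precision.** SE = √([(D′D)⁻¹] × 0.24/30).
- Slope, all 12 units: √(0.774 × 0.008) = 0.079, or 7.9 points per period (8.0 with variance 0.25). The 95% half-width is 1.96 × 7.9 ≈ 15 points per period.
- Intervention coefficient without the slope term: √(1.2 × 0.008) = 0.098.
- Intervention coefficient with the slope term: √(1.394 × 0.008) = 0.106. It then means the effect in the first exposed period.

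**The case against.** The strongest reply is that the criticised model is inferred. The sentence names the effect as its target, lists no model terms and cites a method that is not available here. Its reference to the intervention periods could describe when the effect is tracked, not which units enter the model. The article is condensed, and an analysis plan that is not shown could bring control units in. This has weight, and it is why the point is put as the literal reading. The literal reading is still the more natural one: the same section uses all control and intervention units for the main analysis and then names only the intervention periods for this one. That is a stated choice of data and not detail left for later.

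A second reply is that the Abstract and the Discussion already deal with time effects. The Abstract does so for the comparison between arms, and the Discussion says only that such effects can be included. Neither reaches this analysis, and a period term within intervention units would not cure it (step 1).

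A third reply is that little depends on the result, and this stands in full. Evolution of the effect is not among the objectives in the Background or the outcomes in Outcome measurement. A reader might infer that a misread trend would drive extension of the programme to other facilities. The document does not support that: extension is a conditional remark in the Abstract and Conclusion, tied to a substantial impact on prevention of delirium and not to this series.

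**Conclusion.** The point holds as a limited one. Read literally, the evolution analysis cannot distinguish a changing effect from a secular trend, and a trend of any size would pass in full into the reported slope when ward terms are fitted. Control units are needed to separate the two.

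The rank and bias figures rest on the assumed one-ward-per-step layout, on ward terms being kept, and on the literal reading of which units are used. The standard errors also rest on the planned rates, 30 patients per unit and the risk-difference scale.

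A reader might infer that the trial's main result is confounded with time in the same way. This point does not show that: the main comparison uses all units, and the Abstract promises time effects for it. It would also go too far to say that drift is certain to be misreported, since the sentence does not expressly exclude control units. The analysis should be corrected, but it is secondary to the trial's conclusions.

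**What to change.** Keep the primary model unchanged. Replace the intervention-only series with a separate model on all 12 units containing ward, categorical calendar period, intervention, and intervention × periods since introduction (0, 1, 2). Label it exploratory and report the slope with its confidence interval.

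The interaction should not go into the primary model. It would turn the primary coefficient into the first-period effect and raise its standard error from 9.8 to 10.6 points.

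The change takes a few lines of text and one extra model, with no new data. Two costs should be stated with the result:
- The interval is wide, about ±15 points per period against a planned effect of 20 points, so a slope near zero would not show that the effect is stable.
- Under the assumed layout no control unit exists in period 4. Separation there relies on a period effect common to the wards and a linear effect of exposure time.

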### Ethical consideration

The participating patients will give their verbal informed consent after being told about the study. Their participation or refusal will not affect their medical and nursing care. The study protocol has been reviewed and approved by an ethics committee (Comité de Protection des Personnes Sud-Est IV). All procedures are in accordance with the declaration of Helsinki.

CONFUCIUS study has been registered in the clinical trials (Current Controlled Trials NCT01316965).

